# Telemedicine for Adults With Cochlear Implants in the United Kingdom (CHOICE): Protocol for a Prospective Interventional Multisite Study

**DOI:** 10.2196/27207

**Published:** 2022-04-13

**Keywords:** cochlear implants, hearing, deafness, telemedicine, patient-centered care

## Abstract

**Background:**

Cochlear implants provide hearing to approximately 750,000 people with deafness worldwide; these patients require lifelong follow-up. Care for adults with implants in the United Kingdom occurs at one of 19 centers, which may be far from the patients’ homes. In a previous randomized controlled trial, we successfully introduced person-centered care. We designed, implemented, and evaluated the following remote care pathway: a personalized web-based support tool, home hearing check, self–device adjustment, and upgrading of sound processors at home rather than in the clinic. The remote care group had a significant increase in empowerment after using the tools, and the patients and clinicians were keen to continue. We would now like to scale up these improvements as an option for >12,000 UK adults using implants; we are commissioning an independent evaluation of this intervention and rollout to establish if it achieves its aims of more empowered and confident patients; more accessible and equitable care; stable hearing; more efficient, person-centered, and scalable service; and more satisfied and engaged patients and clinicians.

**Objective:**

This study aims to evaluate the impact and rollout of a person-centered clinical care pathway via telemedicine for adults with cochlear implants in the United Kingdom, using both outcomes and process evaluation.

**Methods:**

This project will scale up and evaluate a person-centered long-term follow-up pathway for adults using cochlear implants through a personalized website, including a home hearing check, uploading photos of cochlear implant site, listening in noise and music practice, ordering of spares, questionnaires, and other resources. Both quantitative and qualitative analyses will be conducted, and they will be both an outcome and process evaluation.

**Results:**

As of July 2021, the trial is closed, and all data collection is complete. The evaluation report is expected to be published in December 2021, and the research data have not yet been analyzed.

**Conclusions:**

This project will present the results of the first scaling up of a remote care pathway for adults with cochlear implants in the United Kingdom.

**Trial Registration:**

International Standard Randomized Controlled Trial Number ISRCTN51668922; https://www.isrctn.com/ISRCTN51668922

**International Registered Report Identifier (IRRID):**

DERR1-10.2196/27207

## Introduction

### Background

Cochlear implants are the most successful of all neural prostheses [1]; they can provide hearing to people with severe to profound deafness. Approximately 1600 people receive cochlear implants in the United Kingdom (UK) each year [2]. The total number of people with implants is approximately 20,000 in the UK (estimated from [2]) and approximately 0.75 million worldwide (estimated from [3-5]). Numbers are likely to increase rapidly, with only approximately 5% of eligible people in the UK and worldwide having received an implant [4,6]. The number of people of retirement age is projected to increase by 28% by 2035 [7], indicating a further increase in the number of people with hearing impairment. Adult cochlear implant care in the United Kingdom is provided at one of 19 tertiary centers involving assessment, surgery, and a resource-intensive acute phase of device adjustment and rehabilitation. When a patient attends a long-term follow-up appointment, the following tasks may be performed: speech recognition testing, device adjustment, rehabilitation, equipment check and troubleshooting, and the provision of replacement or upgraded equipment. Currently, UK implant centers review patients on a clinic-led schedule, which means review appointments that provide little benefit to the patient can occur. Conversely, when some patients attend routine appointments, there is hearing deterioration that the patient had not noticed. This is often remedied by replacing equipment, which the patient could have done at home.

Cochlear implant centers may be several hours away from the patient’s home, necessitating travel expenses, time off work, and family disruption; distance to care is a significant barrier to hearing care worldwide [8]. Making this care pathway person centered instead may provide a more efficient and effective service and allow more timely identification of issues; evidence suggests that person-centered care can improve a range of factors, including patient experience, care quality, and health outcomes, and may help clinics manage a growing number of people with long-term conditions [9].

We previously designed and implemented a remote care pathway for adults with cochlear implants to enable them to perform some of the follow-up tasks themselves at home. We ran a 6-month clinical trial with 60 people randomized to either a telemedicine remote care pathway or a control group who followed their usual appointment schedule [10]. The main outcome evaluated was patient empowerment, which has been shown to be strongly linked to better outcomes in people with long-term conditions. We found that only the remote care group had a significant increase in their cochlear implant empowerment after using remote care tools. The quality of life remained unchanged in the 2 groups. The hearing check results in the clinic improved in the remote care group, although they did not notice a change. However, the control group felt that their hearing had become slightly worse. This may suggest that the remote care group was better able to take action to keep their hearing stable during the trial, or, perhaps, the control group felt they were missing out on a desirable opportunity to take a more active role in their hearing health care.

Discontinuing routine appointments and attending the clinic only when there is a clinical need may provide the following benefits for patients using cochlear implants:

More stable hearing (problems identified and resolved quicker)Better hearing (ability to fine-tune when away from the clinic)Convenience of not traveling for routine appointmentsReduction of travel costs and time, time off work, and disruption to family lifeIncreased confidence in managing one’s own hearingGreater equality in service delivery (same level of service regardless of distance from the clinic)

It may also mean that the clinic has greater resources (time, money, and space) to see both patients with more complex needs and an expanding population of new patients. People using cochlear implants and their families generally like to take a more active role in their care and welcome the use of technology to assist self-care [11,12]. The National Health Service (NHS) has a strong commitment to promoting self-care and self-management [13] for people with long-term conditions [14], with “the vision of a citizen-centred, digitally-enabled, health and social care system” [15]. Evidence shows a significant improvement in outcomes when patients use self-management tools [16], and those who are activated and involved in their care tend to have better health outcomes [17,18]. We are now ready to scale up successful remote care interventions for many more people with cochlear implants in the United Kingdom.

### Objective

This study aims to evaluate the impact and rollout of a person-centered clinical care pathway via telemedicine for adults with cochlear implants in the United Kingdom, using both outcomes and process evaluation.

## Methods

### Project Design and Setting

This is a prospective, interventional, multisite, quality improvement project led and sponsored by the University of Southampton. All research measures will be self-administered on the web or by a paper questionnaire at the patient’s home or other locations of their choice. The staff will complete the measures at work or at a location of their choice. Data collection began when the first site opened on June 11, 2019**,** and continued until January 31, 2021. Clinics will join the study when appropriate local approvals are obtained; therefore, it is likely that the follow-up at each clinic will be for different durations.

### Intervention

This project introduced a remote care pathway option for adults using cochlear implants: cochlear implant home care (CHOICE). We built a personalized, scalable, and responsive web app (not a native application but accessible from any internet browser) based on our previously trialed CIRCA (Cochlear Implant Remote Care website; built in LifeGuide [19]). The app incorporated a home hearing check based on the triple digit test [20], personalized reminders (eg, change microphone cover), rehabilitation exercises (listening in noise, music, and telephone practice), uploading a photo of the cochlear implant surgery site (behind the ear) for review by the clinical care team, information and training, logging the number of hours patients used their cochlear implant (optional and self-reported only), evaluation measures, ordering replacement parts for their cochlear implant, emotional support resources, and questionnaires (Figure 1). The home hearing check provides a screen for whether the patient should come to the clinic based on comparison with a baseline check. Speech perception in noise testing using spoken digits (eg, *one*) has the advantage of digits being highly familiar stimuli usually known by people with even limited language skills. Digit testing requires a closed, set response and is, thus, suitable for self-testing over the telephone or internet [21,22] and has a minimal learning effect [23]. The test correlates well with speech recognition in noise with sentences in people using cochlear implants [24-27].

It is vital that patients remain vigilant in preventing medical issues related to their cochlear implants. This mainly involves appropriate action for ear infections (following the center’s protocol) and checking the site of the implant and skin under the coil magnet. The CHOICE website advises patients to contact their clinical care center with any medical concerns. The web app has the functionality to upload and store photos of the patient’s implant site. Patients will be asked to take a baseline photograph at an early stage to provide a comparison with later images.

The patient’s clinician at their cochlear implant center will have access to their results and web app use in the CHOICE web-based clinician dashboard. Cochlear implant center clinic appointments will be given if required, requested, or indicated by the outputs of the remote care tools. Otherwise, the patients in this pathway will continue with remote care. Participants may access the web app tools as often as they wish.

Automated flagging by email and website notifications will be the cornerstone of the remote care pathway. This will ensure that the patient’s problems are not missed and will provide the most efficient use of clinician time. Some patient flagging situations are as follows: no interaction with CHOICE for 3 months; hearing deterioration; patients who indicate that they need help on the general check-up questionnaire; each time a photo is uploaded, clinicians need to review it; replacement stock items are required; patient reports their daily sound processor use is **<**6 hours; request to leave CHOICE; and freedom of information request.

When an alert is received, the patient’s clinician will decide whether further action is required; for example, an in-center appointment.

The CHOICE website conforms to the following specifications: risk management (ISO 14971:2007) and software life cycle (BS EN 62304:2006) and complies with the requirements of the European Union directive 93/42/ECC for medical devices. It is Conformitè Europëenne marked and registered with the Medicines and Healthcare products Regulatory Agency as a Class 1 medical device.

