**Patients**									
	Patient impact (engagement)	1		Quantitative		CHOICE^a^ web app data: number of log-ins, time spent on CHOICE, uses of self–device adjustment (if appropriate), and uses of home hearing check		All data	
	Patient impact (quality)	1		Quantitative		Number of errors in CHOICE, adverse events, and missed issues		All data	
	Patient impact	1		Quantitative		Survey about use of follow-up care (consequences for travel cost, time, hours off work, and child care [including accompanying person])		Once at patient focus group or interview	
	Patient impact	1		Quantitative		NHS^b^ Friends and Family Test		Minimum of twice: baseline (on registration) and after using CHOICE for several months	
	Patient impact	1		Qualitative		Focus groups		Once: planned but unable to happen because of the COVID-19 pandemic	
	Patient impact	1		Qualitative		One-on-one interviews		Once: for patients who prefer one-on-one interviews or if focus groups cannot occur; toward the end of the project	
	Patient empowerment	2		Quantitative		PAM^c^ questionnaire and CI-EMP^d^ questionnaire		Baseline (on registration) and 6 months following registration or end of the project—whichever comes sooner	
	Patient hearing	2		Quantitative		Home hearing check results		All data	
	Patient change in empowerment, hearing, and quality of life	2		Quantitative		Global ratings of change questionnaire		Baseline (on registration) and 6 months following registration or end of the project—whichever comes sooner	
	Patient health-related quality of life, including hearing	2		Quantitative		HUI3^e^ questionnaire		Baseline (on registration) and 6 months following registration or end of the project—whichever comes sooner	
	Patient health-related quality of life	2		Quantitative		EQ-5D-5L^f^ questionnaire		Baseline (on registration) and 6 months following registration or end of the project—whichever comes sooner	
	Patient preference of service delivery	2		Quantitative		Discrete Choice Experiment questionnaire		Baseline (on registration) and 6 months following registration or end of the project—whichever comes sooner	
	Patient confidence and experience	4 and 5		Quantitative		R-Outcomes surveys		Baseline (on registration) and every 6 months; some participants may choose to complete an optional, shorter questions set more often	

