#### Primary Research Questions

This study attempts to answer the following primary research questions:

Evaluation: What is the impact of the rollout of the new care pathway on users of the program (people with cochlear implants and the staff)?Research: Does the new care pathway increase empowerment for people with cochlear implants while having no detrimental effect on their hearing and quality of life?

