#### Quantitative

Descriptive statistics and graphs will be used to present the data. Data will be displayed visually wherever possible to facilitate sharing with various stakeholders. The significance value will be set at *P*=.05, including Bonferroni corrections for multiple comparisons where appropriate. All repeated-measures data will be compared at baseline and follow-up using analysis of variance to examine any changes in empowerment, hearing, and quality of life in the participants. Surveys will be analyzed at the baseline and follow-up time points using inferential statistical analyses. The choices of participants in the DCE will be subjected to conditional logit model analysis using the *survival* package of the R programming language.

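### The mean change in the home hearing check cannot by itself answer the no-detriment question, because repair of faults present at baseline can offset new losses in other patients

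*Protocol article*

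**What the plan says.** All places are in the protocol article.

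- **Question.** Primary Research Questions asks whether the pathway increases empowerment "while having no detrimental effect on their hearing and quality of life". The article sets no margin or definition of detriment.
- **Measure.** In Table 1 the patient hearing outcome is "Home hearing check results", and the time point covers all data collected. Project Design and Setting adds: "All research measures will be self-administered on the web or by a paper questionnaire".
- **Analysis.** Data Analysis, Quantitative: "All repeated-measures data will be compared at baseline and follow-up using analysis of variance to examine any changes in empowerment, hearing" and quality of life. For hearing this is a comparison of means.
- **Comparator.** Services Outcomes states that no control group undergoes the same measures.
- **Source population.** Background: "when some patients attend routine appointments, there is hearing deterioration that the patient had not noticed", followed by "This is often remedied by replacing equipment, which the patient could have done at home".
- **Clinical use of the check.** Intervention: "The home hearing check provides a screen for whether the patient should come to the clinic based on comparison with a baseline check". This sentence concerns the attendance screen, not the outcome analysis. It matters here because it shows that the patient's own earlier result is the reference.

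**The concern.** The protocol itself says that hidden, often fixable faults exist in the population it recruits from. It describes no equipment or clinic check tied to the baseline home check, so some baselines may be recorded with a fault present. Two consequences follow for a mean change.

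First, a fault repaired after baseline (patients can order parts through CHOICE) is a gain for that patient. In the average it is set against a loss in someone else. Second, a fault that persists from baseline gives no change at all and cannot be seen.

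At stake is the safety half of primary question 2. A mean near zero, or a small gain, could be read as no detrimental effect while an appreciable minority has lost hearing. With no control group on the same measures, there is no other average against which to judge that result.

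**Working it through.** The plan has no figure to reproduce: no sample size calculation was done, and no rates, effect sizes or standard deviations are given. Everything numerical below is illustration.

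**Inputs, all assumed.** Size of a fault or of a new loss, d = 6 dB (the article gives no unit for the check). Error SD of one check, s = 2 dB. Share with a new loss, w = 10%. Share with a fault at baseline, b = 0 to 15%. Proportion of those faults repaired, r = 50% or 100%. Repairs and new losses fall in different patients, and positive change means better. Sample sizes are 200 (assumed) and 1700 (the article's recruitment ceiling).

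**Mean change and its detection**

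Mean change: m = d(br - w). Variance of change: V = 2s² + d²(br + w) - m². Chance of a significant worsening at two-sided 0.05: Φ(-m/√(V/n) - 1.96).

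Example with b = 0, n = 200: m = 6 × (0 - 0.10) = -0.60; V = 8 + 3.6 - 0.36 = 11.24; SE = √(11.24/200) = 0.237; chance = Φ(2.53 - 1.96) = 72%.

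Example with b = 10%, r = 50%, n = 200: m = 6 × (0.05 - 0.10) = -0.30; V = 8 + 5.4 - 0.09 = 13.31; SE = 0.258; chance = Φ(1.16 - 1.96) = 21%.

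| Baseline faults b | Repaired r | Mean change | Chance, n = 200 | Chance, n = 1700 |
|---|---|---|---|---|
| 0 | - | -0.60 dB | 72% | about 100% |
| 10% | 50% | -0.30 dB | 21% | 92% |
| 10% | 100% | 0.00 dB | 2.5% | 2.5% |
| 15% | 100% | +0.30 dB | about 0% | about 0% |

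In every row 10% of patients have lost 6 dB. Offsetting is complete only when br = w with equal sizes; otherwise it is partial or turns into an apparent gain. With d = 3 to 6 dB, w = 5 to 10%, b = 0 to 15% and r = 50 to 100%, the mean runs from -0.60 to +0.60 dB.

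**Would shares do better?**

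Under the same assumptions the SD of an individual change from error alone is √2 × 2 = 2.83 dB, so a 95% test-retest limit is 1.96 × 2.83 = 5.54 dB. A patient with a true 6 dB loss exceeds it with probability Φ((6 - 5.54)/2.83) = 0.564. An unchanged patient exceeds it with probability 0.025, and a repaired patient almost never.

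Share worsened = 0.564w + 0.025(1 - w - br):

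- b = 0: 0.0564 + 0.0225 = 7.9%
- b = 10%, half repaired: 0.0564 + 0.0213 = 7.8%
- b = 10%, all repaired: 0.0564 + 0.0200 = 7.6%
- b = 15%, all repaired: 0.0564 + 0.0188 = 7.5%

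If nobody changed, the share would be 2.5%. The share worsened therefore hardly moves while the mean swings from -0.60 to +0.30 dB. Its standard error at n = 200 is √(0.076 × 0.924/200) = 1.9 percentage points.

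**Does the individual deterioration flag fill the gap?**

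Assume, for illustration only, a 4 dB threshold. A 6 dB loss from a clean baseline is flagged with probability 1 - Φ((4 - 6)/2.83) = 0.76. If the same patient's baseline carried a 6 dB fault that was repaired before the loss, the net change is zero and the probability is 1 - Φ(4/2.83) = 0.08. The flag shares the weakness of the reference.

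**The case against.** The other side has good points.

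- A fault repaired through CHOICE is a real gain and an intended one: the Background lists quicker resolution of problems among the hoped-for benefits. A fault that predates CHOICE and persists is not new harm. The mean is thus a valid net change. This stands. What remains is that a net change does not show how many patients worsened, and the question is about detriment.
- Any mean hides individual spread. True, but here the protocol itself names a mechanism for gains unrelated to absence of loss.
- The article may simply omit how the baseline check is set up, and patients enter after a shared decision in which equipment maintenance is considered. This stands as a limit: the documents do not say that baselines are faulty, only that hidden faults occur and that no verification is described.
- Hearing is also covered by the deterioration flag, the count of missed issues, the global rating of change and the HUI3 hearing domain. These help, but the flag uses the patient's own baseline, the ratings depend on what patients perceive when the problem is unnoticed deterioration, and no method for finding silent missed issues is described.

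A reader might infer more: that the reference is fixed at registration, that repairs and losses cancel, or that the baseline biases the result. The documents do not support these readings. Table 1 attaches registration to the questionnaires and not to this check; no rates are given, so full cancellation is one case in an assumed range; and a repair is a true gain, not an error.

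**Conclusion.** The point holds in a limited form. For the hearing part of primary question 2, an uncontrolled comparison of mean home-check results cannot separate repair of faults already present from absence of new loss. A null or positive mean is correct as a net change but does not establish that no patients lost hearing.

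The size is unknown. With the assumed values, a loss in 10% of patients can appear as anything from -0.60 dB to +0.30 dB, and the chance of detecting it at 200 patients can fall from 72% to 2.5%. At 1700 patients partial offsetting does little damage to detection (92%), but full offsetting is as damaging as at 200. The structural conclusion rests only on the protocol's statement about unnoticed, fixable deterioration and on its choice of analysis. The numbers rest on assumed fault rates, sizes and measurement error.

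**What to change.** In Data Analysis, Quantitative, for the hearing part of primary question 2:

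1. Report beside the mean change the shares of patients improved and worsened beyond test-retest error. Estimate that error from the repeated home checks or state it as an assumption, and give the share expected by chance alone.
2. Base the conclusion of no detrimental effect on the share worsened as well as on the mean.
3. State that stable means relative to the patient's own home baseline, so a fault that persists from baseline cannot be seen.
4. If the date of the last clinic check can still be linked, use it in a sensitivity analysis only. Making recently checked patients the main set would add selection to a study that already warns of it, would remove some of the repair benefit the pathway is meant to deliver, and may require relinking deidentified data.

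The cost is small. The Results section says collection is complete and the research data are not yet analysed, so steps 1 to 3 need only extra analysis and wording. The drawback is that dichotomised shares are less precise than a mean, and they still inherit the unverified baseline.

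### A baseline-versus-follow-up mean of a self-timed hearing check that also screens for clinic review cannot, on its own, support a conclusion that hearing was not harmed

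*Protocol article*

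**What the plan says.** Four parts of the protocol article bear on this.

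- **Timing.** The Intervention section states: "Participants may access the web app tools as often as they wish". No retest schedule is given.
- **Outcome.** In the patient rows of Table 1 the hearing measure is "Home hearing check results", and its time-point entry covers all results. By contrast, PAM, CI-EMP, HUI3, EQ-5D-5L and the global rating of change are set at registration and at 6 months, or project end if sooner.
- **Clinical use.** The Intervention section says: "The home hearing check provides a screen for whether the patient should come to the clinic based on comparison with a baseline check". Hearing deterioration is one of the listed flags. Then: "Cochlear implant center clinic appointments will be given if required, requested, or indicated by the outputs of the remote care tools", and "When an alert is received, the patient’s clinician will decide whether further action is required".
- **Analysis.** The Quantitative section of Data Analysis says: "All repeated-measures data will be compared at baseline and follow-up using analysis of variance to examine any changes in empowerment, hearing", with quality of life completing the list.

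Primary research question 2 asks whether the pathway raises empowerment without harming hearing or quality of life. The Abstract lists stable hearing among the aims. The Introduction names quicker identification and resolution of problems as a potential benefit.

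**The concern.** Table 1 treats hearing as a series of results, and the analysis section treats it as two points. If the analysis section is followed as written, the intermediate checks play no part in the hearing comparison, and the result depends on which self-timed check is called the follow-up. The Limitations section warns that many people may have used CHOICE only very briefly by the end of data collection, so that check could fall days or many months after registration.

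The measure also feeds back into care. A patient whose check worsens, who is flagged and whose problem is then corrected ends with a change near zero. A patient with no second check contributes no change at all. A loss in a small minority is diluted by the stable majority. Each of these mechanisms moves the mean towards no change, which is the answer that would favour the pathway. None of the outcomes in Table 1 counts patients with a deteriorated check or says how long deterioration lasted, although stability and speed of resolution are what the pathway is meant to improve.

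**Working it through.** The plan gives no figure to reproduce here: no sample size calculation, hearing margin, SD, episode rate or retest rate. The finding rests on the text. The arithmetic below shows direction and possible size, and **every input in it is assumed**.

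**1. The passages side by side.**

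| Feature | Hearing check | HUI3, EQ-5D-5L, PAM, CI-EMP |
|---|---|---|
| Time point in Table 1 | all results | baseline and 6 months or project end |
| Who sets the timing | the patient | the schedule |
| Result can prompt clinic review | yes | not listed as such |
| Stated analysis | baseline versus follow-up | baseline versus follow-up |

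The stated analysis fits the right-hand column. For the hearing check it leaves the follow-up value undefined.

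**2. A loss confined to a minority.** Let a share p lose δ and the rest stay stable. The mean loss is p × δ. With p = 0.10 and δ = 1 SD (SD of the change score), it is 0.10 × 1 = 0.10 SD. For a paired test at two-sided 5% (the plan sets 0.05 but not sidedness), the noncentrality is 0.10 × √n:

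| Pairs | 0.10 × √n | Power |
|---|---|---|
| 100 | 1.00 | 0.17 |
| 400 | 2.00 | 0.51 |
| 800 | 2.83 | 0.81 |

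At 100 pairs the 95% CI half-width is 1.98/√100 = 0.20 SD. The protocol gives about 1700 patients as an upper limit and says uptake cannot be predicted, so the number of pairs could lie anywhere in this range or outside it. Even where power is good, a mean loss of 0.10 SD does not show that one patient in ten lost 1 SD.

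**3. Corrected episodes and patients who do not retest.** Let e be the share with an episode of size D, f the share of detected episodes resolved before the last check, and a and b the never-retest shares without and with an episode.

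- Share retested: R = (1 − e)(1 − a) + e(1 − b)
- Unresolved and retested: u = e(1 − b)(1 − f)
- Two-point mean among retesters: D × u / R
- Mean at the end over all patients, if unretested episodes stay unresolved: D × (u + e × b)

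With D = 1.5 SD of test-retest change and a = 0.20:

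| e | f | b | R | u | Two-point mean (SD) | Mean at end, all patients (SD) | Episodes never seen (e × b) |
|---|---|---|---|---|---|---|---|
| 0.10 | 0.80 | 0.20 | 0.80 | 0.016 | 0.03 | 0.05 | 2% |
| 0.10 | 0.80 | 0.50 | 0.77 | 0.010 | 0.02 | 0.09 | 5% |
| 0.20 | 0.95 | 0.50 | 0.74 | 0.005 | 0.01 | 0.16 | 10% |

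A simulation of 200,000 virtual patients per scenario agrees with these values. Over its whole grid (e from 5% to 20%, f from 50% to 95%, b of 20% or 50%) the two-point mean ran from about 0.00 to 0.15 SD.

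**The case against.** The strongest reply has five parts.

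**The analysis sentence is generic.** It covers every scale and does not say that intermediate checks are discarded. The section opens with descriptive statistics and graphs, and follow-up windows are commonly left to a full analysis plan. This is fair as to detail. But the sentence names hearing and fixes a two-occasion comparison for a measure that Table 1 collects without occasions. That mismatch is in the article itself.

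**Patients who never retest are not hidden.** A reader might infer that they vanish from the evaluation. The documents do not support that. Use of the hearing check is a listed outcome, 3 months without interaction raises a flag, and the Missing Data section expects data mostly missing not at random and treats the pattern as informative. What remains is that none of this is tied to the hearing conclusion. A patient who uses other tools but never retests would also not trip the inactivity flag.

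**Other measures cover hearing.** HUI3 and the global rating of change do so at fixed times, and adverse events and missed issues are counted. This stands in part. HUI3 and the global rating are self-reported, while the Introduction describes deterioration that patients had not noticed. In the earlier randomized trial the remote group's clinic hearing checks improved without the patients noticing a change.

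**A flag is not a remedy.** A reader might infer that a poor check automatically leads to correction. The documents say only that the clinician decides. The Background remark "This is often remedied by replacing equipment, which the patient could have done at home" concerns deterioration found at routine appointments under existing care, not a response to a home-check flag. The argument needs only that some flagged problems are corrected.

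**Hearing after detection and correction is a legitimate outcome.** It is, and quick resolution is an intended benefit. For that reason the mean change should stay, with individual deterioration reported beside it.

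**Conclusion.** The point holds in a limited form. The two-point mean is not invalid, but alone it is weak evidence that hearing was unharmed. It is undefined as to the follow-up check, it cannot show episodes that were corrected, and it says little about a loss confined to a minority. The direction is towards no change, provided that some episodes are corrected, or that patients who deteriorate without correction are less likely to have a second check.

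The size is not known. The 10%, 1 SD and number of pairs are assumptions, and the power ranges from about 0.17 to 0.81 between 100 and 800 pairs, so a reader should not conclude that the study is bound to miss such a loss. Nor do the documents show that any deterioration went undetected. The article reports that the research data had not yet been analysed as of July 2021, so on its account the change could be specified before results were seen.

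**What to change.** Reconcile the Table 1 entry for hearing with the Quantitative analysis section, as follows.

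1. **Mean change.** Name the follow-up check as the one nearest 6 months, or project end if sooner, to match the other measures, within a stated window. As a supporting analysis, fit a longitudinal mixed model to all checks, with patient random effects, time since registration and center. State its limits: the timing of checks may be informative, and the model assumes data missing at random whereas the Missing Data section expects otherwise. It does not cure either problem.
2. **Individual deterioration.** From the downloaded checks, using the app's own comparison with baseline, report the proportion of retested patients with at least one deteriorated check, how many returned to baseline, and when. Read this together with testing frequency, since more testing finds more episodes and there is no control group. Work from the check results themselves, because the article does not say that flags are archived.
3. **Patients without a second check.** Beside the hearing result, give the number and share of registrants with no check after baseline, counted as unknown and not as stable.

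Base the hearing conclusion on the mean change and the individual deterioration proportion together.

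The cost is a change to the analysis text, more outputs and a less tidy single answer. No new data collection is needed, since the article says all web app data are downloaded.
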